## Flow Chart with assays (2 analytics nested):

[figure not shown]

### Sample applications:

- 1 Self-collection -----to ❶ POI Card ---- then Split Sample into ❷ PreservCyt (6ml)
- 2 Physician pseudo self-collections – (Inner-Mongolia site only) ❸ Dry Brushes stored Dry for analysis, **Sample A**  $\leq 7$  days; **Sample B** nested analysis  $> 6$  wks
- 1 Physician Direct endocervical collection -----to ❹ PreservCyt (20ml)

### Assay:

- From the ❶ POI Card -----All SeqHPV (5ul HPV DNA); *nested* Cobas (10ul HPV DNA)
- From the ❷ PreservCyt (6ml) -----Cobas (1ml), SeqHPV(1ml)
- From the ❸ Sample A (reconstituted) ---- Cobas (1ml), SeqHPV (1ml)
- From the ❸ Sample B (reconstituted) -----*nested* Cobas (1ml), SeqHPV (1ml)
- From the ❹ PreservCyt(20ml)-----Cobas (1ml), SeqHPV(1ml), and Cytology.

- 6) Patients testing hrHPV positive from any of ❶ - to ❹ will be recalled for colposcopy using the POI protocol of directed and/or random biopsies plus ECC (49).
- 7) Patient management will be determined based on biopsy results and according to current standards at the Peking University Shenzhen Hospital.

### **3.2 Study Population:**

Ten thousand women meeting the enrollment criteria will be recruited for this study from five sites in China, which are selected from 1) Beijing, 2) Shanghai, 3) Shijiazhuang, Hebei Province, 4) Wuhan, Hubei Province, and 5) Wushen County, Erdose, Inner Mongolia.

The enrollment period is expected to begin June 1st, 2016, and be completed by December 31st, 2016. All patient management will be completed by March 31st, 2017.

The study PI intends to give preference to “rural” women. This is a very important distinction in China, since “rural” families who have migrated to the city often find they are outsiders to the economy including the education and healthcare systems.

The research sites are selected to represent: 1) the developed, developing and the undeveloped areas in both the South and North of China. 2) The areas with rural populations recently urbanized and/or still agricultural. 3) Areas with medical resources varying from sufficient to insufficient (medically underserved)

Shanghai was selected because 1) it is one of the most developed cities in China, representing an economically developed area in Southeast China; 2) there is a large recently urbanized rural population; and 3) its per-capital medical resources are among the highest.

Beijing was selected because 1) it is one of the most developed cities in China representing an economically developed area in Northeast China; 2) there is a large recently urbanized rural population and agricultural population; and 3) its per-capital medical resources are among the highest.

Wuhan, the capital of Hubei Province, was selected because 1) it is a typical developing city located in central China and represents the largest settlement of Chinese living in the Yangzi River basin; 2) it has large rural/agricultural population; and 3) it is one of the second line cities with insufficient medical resources.

Shijiazhuang, the capital of Hebei Province, was selected because 1) it is a typical developing city located in Northern China; 2) it has a large rural/agricultural population; 3) it is one of the second line cities with insufficient medical resources.

Wushen County in Erdose, one of the cities in Inner Mongolia Autonomous Administrative Region, was selected because 1) it is one of the undeveloped cities in Northwest China with a

large agricultural population; 2) the HPV infection rate has been reported to be 22%; 3) the majority of the population are rural people working in agriculture and grassland farming; and 4) it is one of the fourth-line cities in China with insufficient (very poor) medical resources.

### **3.3 Data Management and Statistical Methods:**

#### *Data Management*

A strict system of data management will be utilized. All participating women will be assigned a study ID number upon entry into the study. Only the Principal Investigator and Project Coordinators will have access to the complete files matching personal identifiers to the confidential study ID numbers. Laboratory samples and results are identified only by confidential code numbers with no

available personal identifiers. Laboratory information that could in any way be linked to a particular study participant by name or personal identifier will not be released except to provide that patient with needed medical care and appropriate follow-up care. All reports, publications and scientific presentations of the findings from the study will be absent of any personal identifiers, and therefore presented without the identities of individual participants.

Samples are tracked and the study questionnaire and laboratory data will be entered onto the study data forms at the clinical sites. The forms will be copied and the original copy transferred to the data management office at Peking University Shenzhen Hospital to be dual entered into the Study Data Management System. These files will be backed up nightly. All forms will be stored in locked files by the Project Coordinator.

Data management will include quality control procedures including the employing of range checks and assessment of completeness and consistency across variables. The site specific data manager will be supervised by the study assigned epidemiologist and biostatistician. All data will be merged into one cleaned and locked database to create a final set for data analysis.

#### *Data Analysis*

Data analysis will be a collaboration between Preventive Oncology International, affiliated with the Women's Health Institute, the Cleveland Clinic in Cleveland, Ohio, USA and Peking University Shenzhen Hospital, Shenzhen, China.

#### *Statistical Methods*

The primary endpoints of our study will be the sensitivity and specificity of the hrHPV tests for cervical intraepithelial neoplasia (CIN) 3 or cancer (CIN 3+). The secondary endpoints will be the sensitivity and specificity of the hrHPV tests for CIN 2+.

Our estimates of the difference in sensitivity for CIN 3+ and specificity for CIN 3+ that may be detected are based on the prevalence of hrHPV and prevalence of CIN 3+ (the primary endpoint) or CIN 2+ (the secondary endpoint) in the population studied. Our estimates of the prevalence of hrHPV and CIN 3+ are likely more accurate than in many studies as we can use the data from SHENCCAST II (17) as a guide. In SHENCCAST II (17), we screened populations similar to four of our study sites; and our fifth site (Inner Mongolia) has known hrHPV rates and resulting pre-invasive/invasive cervical cancer considerably higher than any sites in SHENCCAST II. Adding the site in Inner Mongolia should compensate for the age difference of 25-59 years (SHENCCAST II) vs. 30-59 years for the current trial (CHIMUST).

As in SHENCCAST II, sensitivities and specificities will be calculated for each hrHPV tests. Logistic regression analysis will be used to generate odds ratios and 95 % CI for factors that may be associated with test results by sampling device.

Sample size calculations to compare the sensitivity and specificity of hrHPV tests are based on the prevalence of hrHPV and the prevalence of the endpoint (CIN 3+ or CIN 2+) in the population. In SHENCCAST II, the prevalence of hrHPV measured in vaginal self-collected or endocervical practitioner-collected samples and tested for hrHPV by MALDI-TOF or Cervista assays was between 11.1% and 14.8%. The prevalence of the primary endpoint of CIN 3+ in SHENCCAST II

was 1.6% (141/8,556) while that of the secondary endpoint of CIN 2+ was 2.7% (227/8,556). The major results from SHENCCAST II are reproduced in Table 1 below. The SeqHPV assay being used in this trial, was trained and tested on SHENCCAST II specimens and showed results similar to MALDI-TOF. (19)

**Table 1: Comparison of the sensitivity and specificity for  $\geq$ CIN 3 of vaginal self-collected and physician collected specimens (endocervical) assayed for HR-HPV by Cervista and MALDI-TOF.**

(95% confidence intervals and the actual patient numbers are in parentheses).

McNemars p-values for the comparison of the sensitivity of self-collected MALDI-TOF to physician collected Cervista is 1.0. McNemars p-value for the comparison for the specificities is  $p < 0.0001$

| SPECIMEN/HR-HPV TEST        | SENSITIVITY FOR <math>\geq</math>CIN 3 (%) (C.I.)(n) | SPECIFICITY FOR <math>\geq</math>CIN 3 (%) (C.I.)(n) |
|------------------------------------|-------------------------------------------------------------|-------------------------------------------------------------|
| Vaginal self-collected / Cervista  | 70.9% (62.7-78.3) (100/141)                          | 86.1% (85.3-86.8) (7248/8415)                        |
| Endocervical / Cervista            | 95.0% (90.0-98.0) (134/141)                          | 90.3% (89.6-90.9) (7598/8415)                        |
| Vaginal self-collected / MALDI-TOF | 94.3% (89.1-97.5) (133/141)                          | 87.5% (86.8-88.2) (7370/8415)                        |
| Endocervical / MALDI-TOF           | 94.3% (89.1-97.5) (133/141)                          | 89.4% (88.7-90.0) (7526/8415)                        |

The 95% CI for the sensitivity of hrHPV in Table 1 spans about 8%, suggesting that, with a study involving 10,000 women with prevalence of hrHPV of 11.1 to 14.8% and prevalence of CIN 3+ of 1.6%, we can reliably detect a difference in sensitivity of about 8%. The 95% CI for the specificity of hrHPV in Table 1 spans only about 1.3% suggesting that we can reliably detect differences in specificity of the hrHPV test greater than 1.3%. As we have paired specimens, the difference in sensitivity for CIN 3+ that can reliably be detected is closer to 7% i.e. 94.3% (133/141) vs. 87.2% (123/141) rather than 8%.

*Primary Objective: Evaluation of the Cobas 4800 Assay, and the SeqHPV Assay for the detection of high grade pre-cancer of the uterine cervix, in population based screening samples obtained using self-collection.*

To evaluate the comparative sensitivities and specificities of the hrHPV platforms, the sensitivity and specificity of each test will be calculated using biopsy showing CIN 3+ (primary endpoint) or CIN 2+ (secondary endpoint) as the gold standards.

*Secondary objective 1: To evaluate differences in assay performance using solid (filter paper cards), dry brush, and liquid based specimen transport for the self-collected and physician collected cervico-vaginal specimens.*

To determine which kind of sample collection media is a suitable medium for collecting and storing vaginal self-samples relative to the assay used we will calculate sensitivities for detecting CIN2+

and CIN3+ and the number of insufficient samples for hrHPV testing of the different sample collection transport systems.

*Secondary objective 2: To evaluate cytology and genotyping as secondary screens after primary hrHPV screening using Cobas and SeqHPV.*

The focus will be to explore practical algorithms that will maximize specificity for CIN 3+ with minimal loss in sensitivity for CIN 3+. Differences in sensitivity and specificity for CIN 3+ will be compared with McNemar's test when there are paired results and Chi-Square when there are independent groups. Cytology will be analysed as a triage technology with a special focus on the non-HPV 16/18 positive population. For the genotyping analysis the available types (14 HPV types) will be used from SeqHPV. Types 16/18 will be used from SeqHPV and Cobas.

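### The 8% (7% paired) reliably detectable difference in CIN 3+ sensitivity is read off one proportion's confidence interval; it holds only under low, nearly one-directional discordance that the protocol never states

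*Protocol*

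**What the plan says.** Sensitivity and specificity for CIN 3+ are the primary endpoints (Protocol 3.3, Statistical Methods). Planning draws on the earlier screening trial SHENCCAST II, where CIN 3+ prevalence "was 1.6% (141/8,556) while that of the secondary endpoint of CIN 2+ was 2.7% (227/8,556"). Table 1 gives self-collected MALDI-TOF a sensitivity of 94.3%, with interval and count "89.1-97.5) (133/141").

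After Table 1 the protocol argues from an interval width. The premise is worded "The 95% CI for the sensitivity of hrHPV in Table 1 spans about 8%, suggesting that" and leads straight to a claim about detectable differences. The planning size is the 10,000 women of this trial at the prevalences seen before. The claim itself is that "we can reliably detect a difference in sensitivity of about 8" percent. It then turns to pairing and says that "the difference in sensitivity for CIN 3+ that can reliably be detected is closer to 7% i.e. 94.3% (133/141) vs. 87.2% (123/141").

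No significance level, sidedness, power or rate of disagreement between tests accompanies either figure. McNemar's test is named for paired comparisons under secondary objective 2.

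**The concern.** The 95% interval around one sensitivity says how precisely that sensitivity is estimated. It does not say how large a true difference between two tests must be before the trial is likely to find it. For paired tests that depends on how many CIN 3+ cases are found by one test and missed by the other, in each direction, and the protocol gives neither number.

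The study compares assays, collection methods and transport media, so a loss of sensitivity is what it is looking for. A reader told that 7 points is reliably detectable could take a non-significant comparison as evidence against a loss of that size. Whether that is fair depends on an assumption the reader cannot see.

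**Working it through.** **Inputs.** From the protocol: 10,000 women, CIN 3+ prevalence 1.6%, reference sensitivity 133/141 = 94.3%, comparator 123/141 = 87.2%. Expected cases: 10,000 x 0.016 = 160. Assumed, because not stated: two-sided alpha 0.05, with 80% and 90% power as benchmarks.

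**1. Where the 8% comes from.** The exact (Clopper-Pearson) interval for 133/141 is 89.1 to 97.5, a width of 8.4 points. For 134/141 it is 90.0 to 98.0, a width of 7.9 points. The figure reproduces as an interval width.

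**2. The 8% as an unpaired difference.** Take p1 = 0.943, p2 = 0.863, pooled p = 0.903, n = 160 per test.
- Standard error under no difference: sqrt(2 x 0.903 x 0.097 / 160) = 0.0331; times 1.96 = 0.0648.
- Standard error under the alternative: sqrt((0.943 x 0.057 + 0.863 x 0.137) / 160) = 0.0327.
- Power = Phi((0.080 - 0.0648) / 0.0327) = Phi(0.465) = 68%.

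With 141 cases it is 62%. Unpaired, 80% power at 160 cases needs about 9.6 points.

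**3. Where the 7% may come from.** The protocol does not explain it. The pair 133 vs 123 of 141 differs by 10 cases (7.1 points). At maximum discordance, when no case is missed by both tests, the discordant pairs are 18 vs 8. Uncorrected McNemar: z = (18 - 8) / sqrt(26) = 1.961, p = 0.0499; exact p = 0.076. One case fewer, 17 vs 8, gives z = 9/5 = 1.80, p = 0.072. So the example coincides with an observed gap that is just significant by the uncorrected test. That this is its origin is an inference.

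**4. The 7% as a paired difference.** Let p01 be the share of CIN 3+ cases that only the less sensitive test finds, and p10 = p01 + 0.0709 the share that only the better test finds. Power is the sum, over all splits of 160 cases into the two discordant cells and the rest, of the probability of each split for which McNemar's test gives p at or below 0.05. Independent misses give p01 = 0.0567 x 0.872 = 4.9%. The maximum is 8/141 = 5.7%.

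| p01 | Exact McNemar power | Uncorrected McNemar power |
|---|---|---|
| 0 | 97% | 99.7% |
| 1% | 85% | 90% |
| 1.4% | 80% | 86% |
| 2% | 74% | 81% |
| 3% | 65% | 74% |
| 4.9% (independent) | 52% | 61% |
| 5.7% (maximum) | 48% | 57% |

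**5. Detectable paired difference.** Same exact test, 160 cases, reference sensitivity 94.3%:

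| p01 | 80% power | 90% power |
|---|---|---|
| 0 | 4.9 points | 5.8 points |
| 1% | 6.6 | 7.9 |
| 2% | 7.8 | 9.3 |
| 3% | 8.8 | 10.5 |
| 5% | 10.4 | 12.3 |

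**The case against.** The main assay comparison on self-collected liquid runs Cobas and SeqHPV on aliquots of the same 6 ml vial, and both are PCR based (Protocol 2 and 3.1). Their misses are plausibly correlated, which lowers discordance and raises power, so leading with 48 to 52% would present the worst end as typical. Against that, only women positive on some sample are recalled for colposcopy (Protocol 3.1, item 6), so a counted case missed by one test was positive on another. That may push discordance up, although with up to four sample types able to trigger recall, two tests on one vial can still share misses. The discordance is unknown, and that is why it has to be stated.

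It is also fair that the primary objective speaks of calculating sensitivity and specificity, for which a precision rationale is acceptable. But the protocol does not claim precision; it claims that a difference can be detected.

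A reader might infer more than the document supports:
- **That the trial cannot detect 7 to 8 points.** At p01 of 1.4% or less, exact power for 7.1 points is 80% or more.
- **That the 94.3% is SeqHPV's result on its own training specimens.** Table 1 gives it for MALDI-TOF. Of SeqHPV the protocol says only that it "was trained and tested on SHENCCAST II specimens and showed results similar to MALDI-TOF", with no sensitivity figure.
- **That Table 1 refutes the 8% through the wide interval for self-collected Cervista.** That assay is not used in this trial, and the other three rows do span about 8 points.
- **That illustrating with 141 cases rather than 160 is an error.** It is conservative.
- **That this passage is the sole rationale for 10,000 women.** Specificity, also a primary endpoint, has its own statement.

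**Conclusion.** The inference is wrong as written: an interval width for one sensitivity is presented as a reliably detectable difference between two tests, and the reduction to 7% for pairing has no stated basis. The printed figures themselves are arithmetically sound; the fault lies in what is concluded from them.

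At 160 CIN 3+ cases and two-sided 5%, the unpaired 8 points has about 68% power. The paired 7.1 points has between 48% and 97% by the exact test, and reaches 80% only if the less sensitive test alone finds no more than about 1.4% of cases (about 2.1% with the uncorrected test). The supportable conclusion is that the claim is unjustified and depends on low, nearly one-directional discordance, not that the trial is underpowered.

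This rests on the assumed alpha and power benchmarks, a reference sensitivity of 94.3%, the protocol's prevalence of 1.6%, and all 160 cases reaching biopsy; incomplete colposcopy attendance would lower power. It should be fixed, but no design, endpoint or analysis has to change.

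**What to change.** Keep 10,000 women. Delete the word reliably, and replace the two sensitivity sentences after Table 1 with one statement that carries its assumptions, for example:

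> With about 160 CIN 3+ cases, two-sided alpha 0.05, the exact McNemar test and a reference sensitivity of 94.3%, the paired difference detectable with 80% power is about 4.9, 6.6, 7.8, 8.8 or 10.4 points (90% power: 5.8, 7.9, 9.3, 10.5 or 12.3 points) if the less sensitive test alone detects 0, 1, 2, 3 or 5% of cases.

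If the team plans the uncorrected test, it should name that test and recompute the figures, so that results from the two are not mixed. The cost is protocol wording, with no added participants. The drawback is that the stated resolution looks less favourable than a flat 7%.

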### **3. Study Design**

#### **3.1 Methods**

This is a multicenter population-based cross-sectional cervical cancer-screening study that will provide screening for 10,000 women who have not been screened for cervical cancer in the past 3 years. The project will be submitted to the Peking University Shenzhen Hospital institutional review board and the IRB of the Cleveland Clinic in Cleveland, Ohio, USA for study approval. In addition the study will be registered with the Chinese Clinic Trial Registry, an international clinical trials registry platform approved by the WHO.

The clinical study consists of 1 self-sampling and 1 direct-sampling on all participants and 2 pseudo-self-sampling on participants in a high risk subset, all the samples will be used for multiple assays followed by referral for colposcopy and biopsy of women with positive test results from self-collection (any one assay), liquid direct collection (any one assay), plus pseudo-self-collection.

- 1) Recruitment of 10,000 patients for screening and participation in the study (Addendum flow chart)
  - Eligibility Criteria: non-pregnant, 30-59 yrs. of age, no screening for at least 3 years, no prior hysterectomy, no prior radiation, and willing to return for positive management if indicated by the primary tests.
  - Exclusion Criteria: Pregnant,  $< 30$  and  $> 59$  yrs of age, screening in the previous 3 years, history of a hysterectomy, pelvic radiation therapy, or not willing to return for positive management if indicated by the primary tests.
- 2) Informed consent

- 3) Demographics
- 4) Patient obtains 1 self-sample placed on the solid media transport card and then the brush (used as a split sample) placed and agitated in PreservCyt Liquid. The card sample will be obtained using the validated “Just for Me”™ kit, which includes a POI brush designed for both self and direct collection, a solid media specimen transport card (POI Card), and an envelope, all bar coded and contained within an outer envelope with language specific and pictorial sampling instructions. The PreservCyt sample will use the same POI brush and the sample will be placed directly into a vial containing 6ml PreservCyt.

- # 1 sample is first rubbed on the POI Card, then the brush agitated in a 6ml PreservCyt (TCT) (the split-sample).

These self-samples transported by card and liquid will be assayed using a) Roche-Cobas 4800 and b) BGI-SeqHPV test.

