- 5) At ALL sites a physician will then place a vaginal speculum so as to directly-collect an endo-cervical sample from each of the participants. The sample is placed in 20ml ThinPrep® PreservCyt® (TCT) Solution (Hologic); ONLY in Inner Mongolia, prior to placement of the vaginal speculum, the physicians will obtain 2 “pseudo self-samples” which are allowed to dry, then placed into plastic bags for testing at ≤7days and >6wks respectively using a) Roche-Cobas 4800 and b) BGI-SeqHPV test.

The direct samples will be assayed using a) Roche –Cobas and b) BGI-SeqHPV.

Cytology using the Hologic I2 imager systems (computer assisted cytology) will used for future research not for patient care in the current study. The primary goal will be to explore secondary triage for the non-16/18, HPV positive women.

**POI Card Management Protocol** – Each card will be manually punched 4 times and placed in a single well in a 96-well plate. Then they are all washed once using 100 microliters sterile water. The water is carefully removed with a sterile fine-tip pipette. The DNA elution is performed in 50 microliters of sterile water at 56°C for 30 min immediately followed by 95°C for 15 min. in a heating block. The 96-well plate containing DNA elution and pieces of card are centrifuged at 4000 rpm for 3 min and the eluted DNA is transferred into a new 96-well plate. (Any required storage will be at -80°C for further use). When performing the assays 5ul of DNA will be used in each well of the 96 well plates for PCR for SeqHPV. 10ul will be used for a nested case control study using Cobas. (It should be noted that this is the standard volume used for SeqHPV, and it has been thoroughly tested and demonstrated to be optimal with > 99% adequate specimens. It was determined in our prior study that 10ul optimized the Cobas Assay when using the POI card.)

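### The primary endpoint is sensitivity relative to CIN 3+ found in women positive on any trial HPV test; it can overstate absolute sensitivity and should be named and bounded accordingly

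*Protocol*

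**What the plan says.** Section 3.3, Statistical Methods, fixes the endpoint: "The primary endpoints of our study will be the sensitivity and specificity of the hrHPV tests for cervical intraepithelial neoplasia (CIN) 3 or cancer (CIN" (cut at the abbreviation). Under the primary objective it adds that "the sensitivity and specificity of each test will be calculated using biopsy showing CIN 3+ (primary endpoint"), with CIN 2+ as the secondary endpoint and biopsy as the reference for both.

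Section 3.1, Methods, fixes who is biopsied. The overview describes "referral for colposcopy and biopsy of women with positive test results from self-collection (any one assay), liquid direct collection (any one assay"), together with positives on the pseudo-self-samples. Item 6, after the assay list, says that women hrHPV positive on any of the four specimen types "will be recalled for colposcopy using the POI protocol of directed and/or random biopsies plus ECC". The random biopsies are thus taken within the recalled women. They do not sample the women who tested negative.

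Item 5 of section 3.1 says of cytology that it is "not for patient care in the current study". The protocol describes no biopsy, follow-up or statistical correction for women negative on all trial tests. It does not call the sensitivity estimates relative or conditional.

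**The concern.** The tests under evaluation select the women who receive the reference standard. A case missed by one test but found by another counts against the first. A case missed by all of them counts against none. This is partial verification, and its effect on each test's sensitivity runs in one direction: upward, or zero if no such case exists.

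The protocol nevertheless names the plain sensitivity of each test as the primary endpoint. The stated aim is large-scale screening by self-collection, so a reader will take the headline figure as the share of all CIN 3+ that the test finds. The design does not identify that quantity. The endpoint, the reference standard and the referral rule are all set in the protocol itself, so the mismatch is not a detail left to a later analysis plan.

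The reference set is also built differently by site. Only Inner Mongolia has dry-brush pseudo-self-samples, and these can trigger recall there.

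**Working it through.** **Inputs from the protocol**
- Women screened: 10,000 (section 3.1).
- Planning prevalence of CIN 3+ from SHENCCAST II: "was 1.6% (141/8,556) while that of the secondary endpoint of CIN 2+ was 2.7% (227/8,556") (Statistical Methods).
- Planning sensitivities: 133/141 = 94.3% against 123/141 = 87.2% (text below Table 1).
- hrHPV positivity of a single test: 11.1% to 14.8%.

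**Reproducing the plan's figures**
- 133/141 = 94.3%. The exact 95% CI is 89.1-97.5, a width of 8.4 points, matching the stated span of about 8%.
- 141/8,556 = 1.65%, given as 1.6%. Then 1.6% x 10,000 = 160 detected cases.
- Positivity from the Table 1 counts: (134 + 8,415 - 7,598)/8,556 = 11.1% and (100 + 8,415 - 7,248)/8,556 = 14.8%. Both agree.

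**Assumptions, because the documents give neither figure**
- Any-test positivity of 20%, hence 8,000 all-negative women (range tried: 14.8% to 25%).
- Residual CIN 3+ risk r in all-negative women of 0.01% to 0.2%.

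**Sensitivity of one test.** With D = 160 verified cases and m = 8,000 x r unverified cases, absolute sensitivity = observed sensitivity x D/(D + m).

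| r | m | Calculation | Absolute sensitivity | Overstatement (points) |
|---|---|---|---|---|
| 0.01% | 0.8 | 94.3 x 160/160.8 | 93.9% | 0.5 |
| 0.05% | 4 | 94.3 x 160/164 | 92.0% | 2.3 |
| 0.1% | 8 | 94.3 x 160/168 | 89.8% | 4.5 |
| 0.2% | 16 | 94.3 x 160/176 | 85.8% | 8.6 |

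Any-test positivity matters little. Between 14.8% and 25%, the overstatement at r = 0.1% runs from 4.8 to 4.2 points.

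**Comparison of two tests.** Both share the denominator D + m.
- Ratio: 133/123 = 1.081 whatever m is, because D + m cancels.
- Difference: 7.09 x 160/168 = 6.75 points with 8 missed cases, and 7.09 x 160/176 = 6.45 points with 16.

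**Specificity.** Starting from 87.5% of 10,000 - 160 = 9,840 women, there are 8,610 apparent true negatives. With 16 missed cases the true value is (8,610 - 16)/(9,840 - 16) = 87.48%. Even with 40 missed it is 8,570/9,800 = 87.45%.

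**The case against.** The strongest reply is that the trial is comparative. The primary-objective paragraph opens by naming comparison of the platforms as its purpose, the sample size rests on a between-test difference, and the protocol never uses the word absolute. This stands as far as it goes: paired comparisons survive almost intact. It does not settle the matter, because the same sentence prescribes each test's own sensitivity, and that unqualified quantity is the primary endpoint.

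A second reply is that the bias may be trivial. An all-negative woman is negative on five results from two collections (SeqHPV on the card, and both assays on self-collected and on direct liquid). This also stands: at r = 0.01% the overstatement is only 0.5 points. But all five are hrHPV DNA tests on the same women, so shared misses are plausible and the design cannot check for them.

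Three stronger readings might be inferred, and the documents do not support them.
- **That the bias threatens the 7-8 point difference the trial is sized for.** A shift of up to 8.6 points in one test's sensitivity is not comparable with a difference between two tests. The difference itself changes by well under one point over the range of missed cases shown.
- **That the plan counts every unbiopsied woman as disease-free.** Table 1 classifies all 8,556 women (141 + 8,415), and section 3.3 says the calculation follows SHENCCAST II. That suggests such a rule, but the protocol does not state one, and it does not describe how the earlier trial verified disease.
- **That the extra Inner Mongolia samples add inflation.** They can only bring in cases that other tests missed, which lowers overstatement there. The problem is inconsistency between sites.

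**Conclusion.** The concern holds for the absolute sensitivity of each test. As the protocol stands, the primary estimate is sensitivity relative to CIN 3+ found among women positive on any trial test, and it can overstate absolute sensitivity. The direction follows from the referral rule alone. The size does not: 0.5 to 8.6 points rests on 160 detected cases, about 8,000 all-negative women and an assumed residual risk of 0.01% to 0.2%. If the tests together miss no CIN 3+, there is no bias.

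The concern does not extend to the ratio of sensitivities between tests run on all women, which is unchanged. The planned 7.1-point difference is only slightly reduced, and specificity moves by less than 0.1 point. The defect lies in how the primary endpoint is defined and in what may be claimed from it. The comparative conclusions are not in danger.

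**What to change.** 1. In section 3.3, where the primary endpoint and the primary-objective analysis are set out, define the estimate as sensitivity relative to CIN 3+ detected in women positive on any trial test. Report it under that name and make no claim of absolute sensitivity.
2. For tests run on all women, report the paired ratio of sensitivities with its 95% CI. Handle the nested specimens (Cobas on the card, and dry-brush Sample B) separately within their own subset, where a simple ratio over all women is not available.
3. Add a table bounding absolute sensitivity over assumed residual CIN 3+ risks of 0 to 0.2% in all-negative women, with the assumption stated beside it.
4. As a sensitivity analysis, drop cases found only by dry brush, so that the reference set is built from the same tests at every site.

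The cost is wording and a few tables. The headline claim becomes slightly less favourable. No extra biopsies and no change to patient care are needed.
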